**Exclusion criteria**

- The patients cannot understand the study procedures
- Have mental health illness, deafness, blindness
- Be participating in other studies related to psychological issues
- Be receiving anxiety or depression treatment.
- Be participating in relaxation therapy such as yoga, meditation, mindfulness, PMR...
- Have a potential treatment (eg. surgery) or personal plans that will prevent them from practising daily during the 6 weeks of the intervention.

1. **Settings**

Participants will be recruited from four public hospitals, Vietnam National Cancer Institute, Hanoi Oncology Hospital in Hanoi, Bach Mai hospital and Nam Dinh general hospital, Vietnam. These hospitals examine and treat patients from the northern and central provinces of Vietnam.

1. **Study sample**

Basing on the study of K. N. Zhou et al. (2015) the effect sizes of anxiety and depression are 1.72 and 0.74, respectively. Thus, the effect size of depression will be used to calculate the sample size. G*power 3.1 software is used with a type 1 error of 5% (α=0.05) and 90% power (β=0.05), two tails, the sample size is 80. The attrition rate in the study of Liao et al. (2018) was 5% after 8 weeks self-practising MCP at home daily. Thus, the final sample size is 84 and each group is 42. The sample size may be adjusted based on the results of the pilot study.

1. **Randomization and allocation concealment**

Blocked randomisation procedures with a 1:1 allocation will be performed by an independent researcher who will not involve any steps of the study. A randomization list will be computer-generated by using the website at https://www.sealedenvelope.com/simple-randomiser/v1/lists. To prevent the investigator from predicting the treatment sequence, a mix of blocks of sizes 4, 6, 8 at random (Efird, 2011) will be used. Besides, blinding both the sequence of blocks and their block size will be applied to be a more effective protection preventing selection bias (Efird, 2011).

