Sequentially numbered, opaque, sealed envelopes will be prepared. To avoid tampering the creator of the envelope will sign on the back of the envelope (Clark et al., 2020). In addition, security measures will include inserting carbon paper into the envelopes to prevent trans-illumination (Clark et al., 2020). The person who creates and keeps the envelopes will be blinded and not be involved in recruiting participants to prevent the ordering of participants into groups (Efird, 2011). The envelopes that contain the names of the assigned group will be given to each patient after they sign the consent form. The envelopes will be opened only after the envelope has been irreversibly assigned to the participants (Doig & Simpson, 2005).

1. **Blinding**

It is impossible to blind participants or interveners because of the nature of the study (Huang et al., 2010). However, research assistants who assess outcome data, data entry and

analysis will be blinded to avoid the risk of assessor bias. The assistants will not participate in any other stage of implementing the program. The participants will be asked not to share their treatment allocation with the research assistants.

1. **Outcome measures and instruments**

Primary outcomes will include anxiety and depression, stress while the secondary outcome will encompass QoL.

Participants’ characteristic data will be collected via a self-designed demographic sheet which will include age, marital status, education level, employment, family income, stage of cancer, frequency of chemotherapy, treatment regimen.

Anxiety, depression and stress will be measured using the short form of the Depression Anxiety Stress Scale (DASS-21) (Lovibond & Lovibond, 1995). The instrument was translated and used in the Vietnamese population with good internal consistency (Cronbach’s alpha of depression subscale 0.72; Anxiety subscale 0.77; and Stress subscale 0.70, overall 0.88) (Tran et al., 2013). It includes 21 items rating scale, 7 items for anxiety (DASS21-A), 7 items for depression (DASS21-D) and 7 items for stress (DASS21-S). A 4-point Likert-type scale ranging from 0 to 3 was designed on each item, thus each subscale had a score from 0 to 21. The higher the score is the more severe is the anxiety, depression and stress.

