FACT-G will be used to assess QoL. It evaluates in functional scales on Social/family well-being (SWB); Emotional well-being (EWB) and Functional well-being (FWB). Each item is scored in one of five categories ‘Not at all’, ‘A little bit’, ‘some what’, ‘Quite a bit’ ‘Very much’. This tool has been translated and validated in Vietnamese by the FACIT system with the Cronbach’s alpha for the scale being 0.89.

1. **Procedure**

Patients receiving chemotherapy meeting research criteria will be identified by four research assistants who are nurses in the chemotherapy units. The research assistants will contact the participants to obtain written informed consent. If patients agree to participate in the study, they will be randomised to the intervention group or the control group. To assess the recruitment capability, the recruitment rate, the consent rate, and refusal rate, the reason for refusal, ineligibility, number of people signing the consent form will be recorded.

Participants will be assessed at 3-time points by an outcome assessor: after randomization, the baseline (T0) will evaluate the demographic form, DASS-21, FACT-G,.After finishing 3 weeks of self-practice intervention (T1) will assess DASS-21, FACT-G, ,after 3 weeks follow-up (T2) will assess DASS-21, FACT-G. After 6 weeks, the attrition rate will be calculated by recording the participants discontinue or loss of contact, and the reasons for drop out. Three weeks after baseline all the patients will return hospital for the next chemotherapy treatment. In the previous studies, timepoints assessed the effectiveness of MI PMR in cancer patients receiving chemotherapy based on the chemotherapy cycle. Yilmaz and Arslan (2015) evaluated PMR on breast cancer for three weeks (one chemotherapy cycle) and Chen et al. (2020) assess the consistency of MI after three weeks of follow-up. The data of T1 and T2 will be collected during hospitalization by the outcome assessor. The outcome assessor will be trained to collect data. The outcome assessor will be blinded to the study groups to collect data and not involve any steps of the study.

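### Four hospitals recruit from one blocked list that is not stratified by hospital, and the protocol does not say how the envelopes are divided, so chance imbalance within hospitals is likely if the list is used in order of arrival

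*Protocol*

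**What the plan says.** Under Settings: "Participants will be recruited from four public hospitals". They are a national cancer institute, a city oncology hospital, a further large hospital and a general hospital. Under Procedure, eligible patients are "identified by four research assistants who are nurses in the chemotherapy units".

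Under Randomization and allocation concealment: "Blocked randomisation procedures with a 1:1 allocation will be performed by an independent researcher", and "A randomization list will be computer-generated" with a named web tool. The list is in the singular and no stratification factor is given. The same section gives the blocks as "a mix of blocks of sizes 4, 6, 8 at random" and in the next sentence states that "blinding both the sequence of blocks and their block size will be applied".

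On concealment: "Sequentially numbered, opaque, sealed envelopes will be prepared". Nothing says whether the four hospitals share one series or each receives a portion.

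Hospital is not among the participant characteristics listed under Outcome measures and instruments. Data analysis names a t-test or Mann–Whitney test and a GEE model, none with a hospital term.

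**The concern.** A single blocked list balances the arms over the whole trial, not within each hospital. Case mix, regimens and usual care may differ between these hospitals, and usual care, delivered by local staff, is the comparator. With about 21 patients per site, a lopsided split at one hospital would leave a reader asking whether a difference in mood or quality of life reflects the intervention or the hospital. If hospital is neither recorded nor modelled, the stated plan cannot answer.

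A SAP could add a covariate later. It cannot stratify a list that is already in use or settle how the envelopes are divided, so those choices belong in this section and must be fixed before the first allocation.

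**Working it through.** **Inputs from the protocol.** Four hospitals; 84 patients (80 before attrition); 1:1 allocation; blocks of 4, 6 and 8 in random order; d = 0.74; two-sided α = 0.05; 90% power.

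**Assumptions, since the protocol is silent.** Intake per hospital (21 each, with unequal intake as a variant), how envelopes are issued, and the share of outcome variance due to hospital (the ICC).

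**1. The plan's own figure.** With 40 per arm, the noncentrality is 0.74 × √(40/2) = 3.31 on 78 df, giving power 0.905. The stated 80 reproduces at 90% power, and 80 × 1.05 = 84.

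**2. Balance within hospitals.** Lists for 84 patients were simulated with 21 per hospital. A 13:8 split is an arm difference of 5; a 14:7 split is a difference of 7.

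| How allocations reach the hospitals | P(at least one site 13:8 or worse) | P(at least one site 14:7 or worse) |
|---|---|---|
| One list, order of arrival | 71% | 38% |
| One list, consecutive runs of 21 | 2% | 0% |
| Separate list per hospital | 0% | 0% |

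A repeat of the first row with 20,000 lists gave 71.5% and 38.7%.

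Letting site totals vary at random, the chance of a 2:1 or worse split somewhere is:
- One list in arrival order: 34% with equal expected intake, 53% with intake of 40/30/20/10%.
- Separate lists: 0% and 8%, the 8% coming from the smallest site.

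**3. Error rates.** N = 80, equal hospitals, 6,000 runs per scenario.
- Unadjusted t-test, one list in arrival order, ICC 0 to 0.20: type I error 0.052 to 0.058. The highest value occurs at ICC 0, where the t-test is exact for normal data, so the excess is simulation noise. Power is 0.91 to 0.92.
- ICC 0.10: power 0.909 unadjusted on one list, 0.928 with stratification and adjustment.
- ICC 0.20: 0.920 against 0.956.
- Stratified but not adjusted: type I error falls to 0.038 at ICC 0.10 and 0.035 at ICC 0.20, so the test becomes conservative.

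**4. Precision by formula.** If hospital explains 10% of the variance and is adjusted for, the effective d is 0.74/√0.90 = 0.780. The noncentrality is 0.780 × √20 = 3.49 and power is 0.931, against 0.905.

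**5. Printed block sizes.** A guesser with the full allocation history is right 67.9% of the time knowing the sizes and 67.8% without them. About 2.4% of allocations become certain. A recruiter on a shared list who sees only her own hospital's history, and guesses the under-represented arm, is right 51.8% of the time.

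**The case against.** The strongest reply is that the imbalance depends on something the protocol leaves open. If each hospital receives a consecutive run of envelopes, cutting the list does little damage: only the blocks at the joins are split, and 13:8 or worse falls to about 2%. This stands. The 71% holds for use in order of arrival only, and the protocol needs to say which applies.

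A second reply is that Data analysis compares differences between baseline and T1 or T2. Read as change scores, these cancel stable hospital differences in mood or quality of life. This also stands in part: only differences between hospitals in change would remain, so the precision gain may be smaller than step 4 shows.

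Third, a hospital covariate could properly be left to a SAP, which may exist but is not at hand. That is fair for the model term alone. It does not reach the list, the envelopes or the recording of hospital.

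A reader might also infer that printing the block sizes lets recruiters predict allocations. The calculation does not support this, nothing in the protocol says the recruiting nurses work from this text, and envelopes are opened only after irreversible assignment. The contradiction in wording is real; its practical effect is negligible.

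**Conclusion.** The point holds as a design improvement. Four hospitals, one unstratified list and no rule for dividing the envelopes make a visible imbalance at some hospital likely (about 71% for 13:8 or worse, 38% for 14:7 or worse) if the list is used in arrival order with 21 patients per hospital.

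A reader might go further and conclude that hospital differences could bias the treatment effect or produce a false positive. That is not supported. Allocation is still random, the test's error rate already covers chance imbalance, type I error stays near 5%, and the planned 90% power and the sample size stand. What is lost is balance between hospitals and modest precision: 2.6 points of power (90.5% to 93.1%) if hospital explains 10% of outcome variance. The documents give neither that share nor the intake per hospital.

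**What to change.** Before allocation starts:

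- Generate a separate blocked list and a separately numbered envelope set for each hospital, and say so in the protocol.
- Record hospital with the participant characteristics.
- Include hospital as a fixed factor in the GEE and in the between-arm comparison. Stratifying without adjusting makes the test conservative.
- Minor edit: state only that block sizes vary at random, and move the sizes 4, 6 and 8 to a restricted document, in line with the statement that block size is blinded.

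The cost is a few minutes in the same web tool and 3 degrees of freedom. Incomplete blocks at four sites can also leave a small overall imbalance: the simulated mean arm difference was 1.6 (largest 8) with four lists, against 0.6 (largest 4) with one. Smaller blocks within hospitals would limit this.

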**Hypothesis**

- The participants receiving MCP will have a significantly lower level of anxiety compared to the control group.
- The participants receiving MCP will have a significantly lower level of depression compared to the control group.
- The participants receiving MCP will have a significantly lower level of stress compared to the control group
- The participants receiving MCP will have significantly higher QoL scores compared to the control group.

1. **Study design**

A 2-arm, assessor-blinded randomised controlled will be conducted. Randomized Controlled Trial (RCT) is the best design to confirm an objective assessment of the true benefits of medical interventions (Doig & Simpson, 2005). The design will follow the Standard Protocol Items Recommendations for Interventional Trials (SPIRIT) (Chan et al., 2013) .

1. **Participants**

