**Fig. 2. The Consolidated Standards of Reporting Trial (CONSORT) flow diagram (Schulz et al., 2010)**

1. **Intervention fidelity**

Contamination will be minimized by asking the participants not to share the intervention information with other patients. The research assistants will be chosen to participate in the study if they have a bachelor’s degree or a higher qualification, a minimum five-year experience in oncology and have research experience. They will be trained in the data collection process, interview skills to ensure consistency. Only one intervener will deliver MCP training to the patients. The intervener was trained and received music therapy and PMR certificates. To ensure adherence to intervention protocol, the written intervention manual, the checklist will be used. To prevent loss of contact, at least two phone numbers of the patient and the patient's family will be saved.

1. **Data analysis**

Statistical analysis SPSS version 25 will be used, and an intention-to-treat analysis will be used in line with the CONSORT statement. The chi-squared test or Fisher’s exact test, wherever appropriate will be used for categorical data (e.g. family income, cancer stage), while the continuous variables (e.g. age) will use the independent T-test to test the homogeneity at baseline between groups. Categorical variables will be reported as frequencies and percentages and continuous variables will be presented as mean± standard deviation. A two-tailed, two-sample T-test (normally distributed) or Mann–Whitney *U* test (non-normally distributed) will be used to compare the mean difference of DASS-21, FACT-G and subscales score of Intervention Group and Control Group between baseline (T0) and T1, T2, respectively. Cohen’s d will be used to measure the intervention effect size on anxiety and depression, stress, QoL of Intervention Group and Control Group. A generalized estimating equation (GEE) model will be used to compare the difference in each outcome across different time points.

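### Three unranked primary outcomes, each compared at two visits with no primary time point, hierarchy or alpha split, while the sample size spends the full 5% on one depression test

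*Protocol*

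**What the plan says.** Under Outcome measures and instruments: "Primary outcomes will include anxiety and depression, stress while the secondary outcome will encompass QoL". The three primaries are the DASS-21 subscales, and none is ranked first. The Hypothesis section gives each outcome a separate superiority claim; for stress it reads "The participants receiving MCP will have a significantly lower level of stress compared to the control group".

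Data analysis plans t-tests or Mann-Whitney tests to "compare the mean difference of DASS-21, FACT-G and subscales score of Intervention Group and Control Group between baseline (T0) and T1, T2, respectively". It then adds: "A generalized estimating equation (GEE) model will be used to compare the difference in each outcome across different time points". Neither analysis is called primary, and neither visit is called primary.

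Study sample reports that "the effect sizes of anxiety and depression are 1.72 and 0.74, respectively", and continues: "Thus, the effect size of depression will be used to calculate the sample size". The inputs are "type 1 error of 5% (α=0.05) and 90% power (β=0.05), two tails, the sample size is 80", raised to 84 (42 per group) for 5% attrition. Stress does not enter this calculation. The section also allows the sample size to be revised after the pilot.

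The Procedure section describes T1 as the assessment after three weeks of practice and T2 as following a further three weeks, intended to show whether the effect persists.

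**The concern.** Three co-equal primary outcomes at two visits make six primary group comparisons before the GEE models are counted. The only alpha in the protocol is the 5% used for sizing, and that calculation covers one comparison. Nothing says whether one success is enough, whether all three outcomes must succeed, or which visit decides.

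Two things are at stake. First, a significant result on one subscale at one visit could be presented as a primary success, with a false-positive chance well above one in twenty. Second, the sample size leaves no room to repair this later by dividing alpha: any split lowers power below the planned 90%, even for the outcome the trial was sized on. For stress, no stated assumption supports a power claim at all.

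**Working it through.** **1. The plan's own figure.** Inputs from Study sample: d = 0.74, two-sided alpha 0.05, power 90%; the Randomization section gives 1:1 allocation.
- Normal approximation: n per arm = 2(1.960 + 1.282)² / 0.74² = 38.4, so 39.
- Noncentral t: 39.4, so 40 per arm, **80 in total**. This reproduces the plan.
- Power at 40 per arm is 90.5%.
- Attrition: 80 × 1.05 = 84, as stated.
- The printed β of 0.05 does not match 90% power and would need 49 per arm (98). The figure of 80 belongs to β = 0.10.

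So 80 is the size for one test at the full 5%.

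**2. Familywise error if the tests were independent.**
- Three tests: 1 − 0.95³ = 14.3%.
- Six tests: 1 − 0.95⁶ = 26.5%.

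**3. Correlation between subscales.** The protocol gives none, but its Cronbach's alphas (0.72, 0.77, 0.70; overall 0.88) imply one. With mean inter-item correlation r = α / (k − (k−1)α):
- Depression: 0.72/2.68 = 0.269. Anxiety: 0.77/2.38 = 0.324. Stress: 0.70/2.80 = 0.250. Mean 0.281.
- All 21 items: 0.88/3.40 = 0.259.
- There are 210 item pairs, 63 within subscales and 147 between. Mean between-subscale item correlation = (0.259 × 210 − 0.281 × 63)/147 = 0.249.
- Correlation of subscale scores = 49 × 0.249 / (7 + 42 × 0.281) = **0.65**.

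**4. Correlation between visits.** This is assumed. Changes to T1 and to T2 share one baseline. If all three time points are equally correlated at r, the correlation of the two changes is (1 − r) / (2(1 − r)) = 0.5.

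**5. Familywise error with correlated tests.** Simulated two-sided z-tests under no effect, each at 5%:

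| Setting | Error |
|---|---|
| 3 outcomes, one visit, subscale correlation 0 / 0.5 / 0.7 / 0.8 | 14.2% / 12.5% / 10.9% / 9.8% |
| 3 outcomes, two visits, subscale 0.65, visit 0.5 | 20.0% |
| Same, visit correlation 0 to 0.8 | 21.5% to 17.2% |
| 3 outcomes, two visits, both correlations 0.3 to 0.8 | 24.9% to 14.9% |

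Simulated change-score t-tests with 40 per arm and subscale correlation 0.65 gave 20.1% to 20.8% for correlations of 0.3 to 0.7 between time points.

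**6. Cost of splitting alpha later** (depression, d = 0.74):

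| Alpha | Power at 40 per arm | N for 90% power | With 5% dropout |
|---|---|---|---|
| 0.05 | 90.5% | 80 | 84 as planned |
| 0.05/3 | 80.4% | 102 | 108 |
| 0.05/6 | 72.5% | 116 | 123 |

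**7. Stress.** No effect size is given. At 40 per arm and an unadjusted 5%, assumed d of 0.3, 0.4, 0.5 and 0.6 gives power of 26%, 42%, 60% and 75%. Power of 90% needs an effect of about 0.74.

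**The case against.** The strongest reply is that the missing adjustment is read from silence. Data analysis sets no significance threshold and does not say that adjustment is omitted; multiplicity procedures often sit in the SAP, which is not shown. That stands as a limit: a reader might infer that the protocol declares six unadjusted 5% tests, and it does not. It does not remove the point, because the three co-equal primaries and a sample size built on the full 5% are fixed in the protocol itself, and an alpha split added later would cost the power shown above.

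Second, no rule says that one success out of six is enough. The familywise figures describe that reading only. For a single hypothesis at a single visit the error stays at 5%, and an all-must-succeed rule at one named visit would bring no inflation. The protocol states neither rule.

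Third, T2 has a distinct persistence purpose, so the primary family may be three tests rather than six. This is fair, and it is why the one-visit range of 10-14% is given beside the two-visit range. Even that lower range is at least about twice 5%.

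Fourth, the pilot may lead to a revised sample size and would supply stress data. That could repair the stress assumption. The provision does not mention multiplicity.

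**Conclusion.** The point holds in conditional form. As written, the protocol does not secure a 5% error across its primary outcomes. If each test is run at 5% and any one success is claimed, the error is roughly 10-14% at one visit and 15-25% over two visits.

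A reader might infer a flat one-in-five false-positive rate. The documents do not support that as a fixed figure: 20% requires the subscale correlation of 0.65, derived from alphas quoted for a Vietnamese validation population, and an assumed between-visit correlation of 0.5. The independence value is 26.5%.

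A reader might also infer that 90% power is reached for depression alone. That goes too far, since anxiety has near-100% power at the plan's assumed d of 1.72. What is not established is power for stress.

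**What to change.** - Name T1 (week 3) as the primary time point and T2 as the secondary persistence assessment, in line with the Procedure section. One exclusion criterion speaks of six weeks of intervention, whereas Procedure describes three weeks of practice and three of follow-up; these passages must be reconciled when T1 is defined.
- Test at T1 in a pre-specified fixed sequence, each step at two-sided 0.05: depression, then anxiety, then stress. Say which analysis supplies these tests.
- State that the 90% power is for depression at d = 0.74 at the full 5%, that anxiety has more power at the assumed d = 1.72, and that power for stress is not established.

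Depression goes first because the trial is sized on it. Starting with anxiety looks safe at d = 1.72, but the protocol's own pooled anxiety effect for music alone is 0.29, where 40 per arm gives only 25% power. That step could then block the outcome the trial was sized on.

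The cost is wording, with no extra patients. The downside is that a failed step ends confirmatory claims on later outcomes: at d = 0.74 depression fails about 9.5% of the time (1 − 0.905), and at d = 0.5 about 40% (1 − 0.60). T2 results become supportive. Power for anxiety and stress is also conditional on the earlier steps succeeding.

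### Baseline DASS-21 and FACT-G are taken after randomisation, and no rule ensures that unblinded patients complete them before learning their group

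*Protocol*

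**What the plan says.** All references are to the protocol's full-scale study unless stated otherwise.

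- **Procedure.** Randomisation follows directly on consent: "If patients agree to participate in the study, they will be randomised to the intervention group or the control group". The first assessment comes next: "after randomization, the baseline (T0) will evaluate the demographic form, DASS-21, FACT-G".
- **Randomization and allocation concealment.** "The envelopes that contain the names of the assigned group will be given to each patient after they sign the consent form". On opening, the only condition is this: "The envelopes will be opened only after the envelope has been irreversibly assigned to the participants". Completion of T0 is not mentioned.
- **Blinding.** "It is impossible to blind participants or interveners because of the nature of the study". Also: "The participants will be asked not to share their treatment allocation with the research assistants". The second sentence presumes that patients know their group.
- **Procedure, on the assessor.** "The outcome assessor will be blinded to the study groups to collect data and not involve any steps of the study".
- **Data analysis.** A t-test or Mann–Whitney test will "compare the mean difference of DASS-21, FACT-G and subscales score of Intervention Group and Control Group between baseline (T0) and T1, T2, respectively". A GEE model across the time points is also planned.
- **Intervention development, appraisal step.** The first meeting with the intervener takes place once the baseline assessments are finished.
- **Table 3.** It shows a Week 0 baseline column but does not place randomisation. The flow diagram is not reproduced in the text available.

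The pilot study is to use a similar procedure, so the same order applies there.

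**The concern.** A baseline value should be one that allocation cannot have influenced. Here the three primary outcomes (anxiety, depression, stress) and the secondary outcome (quality of life) are the patient's own answers about her current state. News of which group she is in could plausibly move those answers. Blinding the assessor does not help, because the assessor only collects what the patient reports.

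T0 is one half of every change score. If the two arms differ at T0 because of their reaction to allocation, and the reaction has faded by T1, that difference appears in the estimated treatment effect. The planned homogeneity tests at baseline could not tell such a shift from chance imbalance. No measurement taken before allocation would exist to settle the question afterwards, and an analysis plan written later could not supply one.

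**Working it through.** **1. The order of events.** Together, the sections give: eligibility, consent, randomisation with the envelope given to the patient, T0, intervener meeting, three weeks of practice, T1, T2. T0 precedes all contact with the intervention. Nothing in the text places it before the envelope is opened.

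**2. The plan's own sample size.** From the study sample section: d = 0.74, two-sided α = 0.05, power 90%. The noncentral-t calculation gives 39.36, so 40 per arm and 80 in total, as stated. Power at 40 per arm is 0.905. (The section prints β as 0.05; the figure of 80 fits β = 0.10. That is a separate matter.) No stated figure is in dispute here, and moving T0 would not change N.

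**3. Bias in the change score.** Let *b* be the between-arm difference in T0 caused by knowing the allocation, in outcome SDs, and let *p* be the fraction of it still present at T1.

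- Bias in the change-score effect has size b(1 − p).
- If p = 0 (fully transient), the bias is the whole of b. If p = 1 (persists equally), it is zero.

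**4. Assumptions for the illustration (not from the documents).** 40 evaluable per arm; equal variances; T0–T1 correlation r = 0.5; b = 0.1, 0.2 or 0.3. The SD of a change score is √(2(1 − r)) = √(2 × 0.5) = 1 outcome SD, so d = 0.74 applies unchanged. The noncentrality parameter is (effect) × √(40/2) = (effect) × 4.472, with 78 degrees of freedom and critical value 1.991.

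**5. Direction.** Higher DASS-21 scores are worse. Disappointed controls would start higher and then seem to improve more; hopeful intervention patients would start lower and seem to improve less. Either transient reaction biases the change score against the intervention, so the apparent effect is 0.74 − b.

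| b (SD) | Apparent effect | Noncentrality | Power |
|---|---|---|---|
| 0 | 0.74 | 3.309 | 90.5% |
| 0.1 | 0.64 | 2.862 | 80.7% |
| 0.2 | 0.54 | 2.415 | 66.5% |
| 0.3 | 0.44 | 1.968 | 49.3% |

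**6. No true effect: two-sided rejection rate (nominal 5%).**

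| b (SD) | Change score, fully transient | Change score, half persists (bias b/2) | Baseline-adjusted, fully transient |
|---|---|---|---|
| 0.1 | 7.3% | 5.6% | 5.7% |
| 0.2 | 14.3% | 7.3% | 8.0% |
| 0.3 | 26.3% | 10.2% | 11.9% |

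In the last column the bias is r × b and the residual SD is √(1 − r²) = 0.866. At b = 0.2 the standardised bias is 0.5 × 0.2 / 0.866 = 0.115.

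**7. Sensitivity to the correlation.** Over r = 0.3 to 0.7 with a fully transient shift, the change-score error ranges over 6.6–8.8%, 11.6–20.7% and 20.1–40.2% for the three values of b. With baseline adjustment the ranges are 5.2–7.2%, 5.9–13.9% and 7.0–25.5%.

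**8. Which way the false rejections point.** Under the reactions in step 5, almost all rejections in step 6 favour control. For the change score with a fully transient shift, the chance of a false finding in favour of the intervention falls from 2.5% to 0.8%, 0.2% and 0.05%.

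**The case against.** Several parts of the opposing case stand, and they limit what can be claimed.

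- **Knowledge of the group at T0 is not stated.** A reader might infer that every patient knows her group when she fills in the T0 forms. The envelopes are sealed and opaque, the moment of opening relative to T0 is not written, and the flow diagram is not available. The text supports only the statement that the protocol does not prevent it.
- **T0 precedes the intervention.** This is correct. The exposure is limited to a reaction to the group name and does not include treatment.
- **The bias needs a fading reaction.** A reaction that persists equally cancels, and one that half persists has much less effect.
- **Inflated false claims of benefit.** A reader might infer these from the error rates. The likeliest reactions, disappointment in controls and hope in the intervention arm, work the other way and mainly cost power. False claims of benefit would need the opposite reaction.
- **Loss of randomisation.** A reader might infer that the whole comparison is compromised. It is not: assignment and concealment are intact, and the between-arm differences in T1 or T2 scores alone remain randomised comparisons. Only the use of T0 as a reference is affected.
- **Patients who know their group meet the assessor.** This happens at T1 and T2 in any trial with unblinded participants and is not a defect of T0.

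None of this removes the point. The written order puts the allocation in the patient's hands before T0 without a safeguard, and nothing in the protocol explains why that order is needed.

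**Conclusion.** The point holds as a gap in the procedure. The protocol measures the reference value for its change-score analysis after randomisation, in unblinded patients, on self-reported scales, and does not ensure that this happens before they learn their group.

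The possible consequence runs from negligible, if the reaction is small or persists to T1, to serious. A fully transient shift of 0.2 SD would take power from about 90% to about 66%, or the two-sided error from 5% to about 14%. These figures rest on the assumed shift, on its fading, on 40 per arm and on a correlation of 0.5. The documents give no basis for the size or direction of any shift. Baseline adjustment reduces the effect of a transient shift but does not remove it. The order should be corrected before recruitment, because a baseline free of knowledge of allocation cannot be recovered for patients already enrolled.

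**What to change.** In the Procedure and the Randomization and allocation concealment sections, and in the flow diagram, state the order as follows: eligibility; written consent; demographic sheet, DASS-21 and FACT-G (T0) completed and handed in; and only then the next numbered envelope assigned and opened. In the Procedure sentence on T0, change the timing from after to before randomisation. In Table 3, mark randomisation after the Week 0 assessments. Apply the same order in the pilot.

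The cost is a few sentences and one table entry, with no added patients, assessments or change in sample size. The one drawback is that a few patients may complete T0 and then not be randomised; they should be counted in the recruitment record.
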